### Outcomes

#### Demographic Variables

Participants will be asked to complete an anonymous survey of various demographic data, which will include the following: age, gender (“Male,” “Female,” “nonbinary,” and “transgender”), country of residence (“Ghana” and “Kenya”), type of FHWs (3 specified categories will be provided as these are most common: “Medical Doctor,” “Nurse,” “Community Health Worker,” and “Other” under which participants will be asked to add their own category), frequency of dealing with skin NTDs [“Rarely (<1 case/month),” “Occasionally (1-3 cases/month),” “Frequently (4-6 cases/month),” and “Usually (>6 cases/month)”], experience and training in dermatology (“Trained and experienced,” “Not trained but with experience with dermatology patients,” and “Neither trained nor experienced”), work environment (“rural” and “urban”), working institution (“Public healthcare setting,” “Private healthcare setting,” and “NGO”), knowledge of mobile technology (“High—I’m able to use mobile technologies without having many issues,” “Medium—I’m able to use mobile technologies but sometimes I need some help,” and “Low—I’m not able to use mobile technologies without supervision and help”), and languages (open answer for participants to enter the languages they can speak).

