As the developers of Skin NTDs App have ambitious plans and expectations, it is essential to conduct a rigorous and validated assessment of this app. This paper describes the protocol for a cross-sectional study aimed to assess the engagement, functionality, aesthetics, and quality information for the real end user in their actual context of version 3 of Skin NTDs App in accordance with a validated tool. In addition, a secondary goal of this study will be to determine whether any of the demographic information collected has an impact on the final uMARS score, since the developers of Skin NTDs App do not intend to customize the app when implementing it in any setting.

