### Participants and Eligibility

All FHWs who deal with skin NTDs in both selected countries on a daily basis, are responsible for the diagnosis and management of skin NTDs, who own a smartphone device (Apple or Android), and have downloaded Skin NTDs App and used it on at least 5 different days for at least 10 minutes each day are considered eligible. Moreover, participants will need to have access to email or WhatsApp to provide informed consent.

Exclusion criteria are a low comprehension of the English language and refusal to sign the informed consent form.

The target population is the same for both parts of the study. Participants will be asked to read the information sheet (for more detail, see Multimedia Appendix 1) before signing the informed consent form.

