### Sample Size Calculation

Sample size was calculated on the basis of the 6 stages of the intervention maturity life cycle described by the WHO in *Monitoring and Evaluating Digital Health Interventions* [17], a schematic and practical guide to know which have to be the goals in each stage, how many participants are required, and which are the measurement targets.

Skin NTDs App is currently in the prototype phase, which corresponds to stages 1 and 2 of the 6 stages of the intervention maturity life cycle, according to WHO guidelines. As a result, the WHO advises testing it with a sample size of between 10 and 100 users.

Taking into account that 100 is the maximum recommended number of participants and the web-based modality of this study, we assume a dropout rate of 50%. These calculations leave a final sample size of 50 participants.

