## Results

The results of this work are expected during the third quarter of 2022. First, Skin NTDs App version 3 is expected to obtain a result of >3 out of 5 points on the uMARS. In addition, it is expected that the results will not show any difference by sex, type of work environment or working institution, or country. However, it is suspected that those variables related to experience in dermatology or the use of mobile technology may be determining factors when evaluating the user experience with the App. On the other hand, the perceptions collected from the semistructured interviews are expected to be the element to understand the reason for the results obtained on the uMARS.

Moreover, they will be the previous step before assessing other aspects of the App, such as the efficiency, how it should be disseminated or implemented, etc.

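### The dermatology question has no answer for workers who are trained but not experienced, so any such respondent is misplaced on one of the two suspected determinants of the uMARS score

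*Protocol article*

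**What the plan says.** The protocol article, under Demographic Variables, describes a single item on dermatology background and prints its answers in full: "experience and training in dermatology (“Trained and experienced,” “Not trained but with experience with dermatology patients,” and “Neither trained nor experienced". No open answer is listed for it. The same section does give one for type of health worker: "Other” under which participants will be asked to add their own category".

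The item serves a stated aim. The Introduction sets as a secondary goal to "determine whether any of the demographic information collected has an impact on the final uMARS score". The Results section expects no difference by sex, work environment, institution or country, but voices this suspicion: "those variables related to experience in dermatology or the use of mobile technology may be determining factors when evaluating the user experience with the App". The abstract names the same two factors.

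Two other statements bear on how many respondents could be trained but inexperienced. Participants and Eligibility admits "All FHWs who deal with skin NTDs in both selected countries on a daily basis" who are also responsible for diagnosis and management. Yet the caseload item under Demographic Variables starts at "Rarely (<1 case/month").

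**The concern.** Training (yes/no) and experience (yes/no) make four combinations, and the item offers three. A recently trained worker who has seen few dermatology patients has no true answer. That worker must choose a level that is wrong on training, wrong on experience or, for the middle level, wrong on both, or else leave the item blank.

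Such answers look valid in the data set, so the analyst cannot tell which are misplaced. The article prints the answer list in full, so this is not a detail lost in condensing, and a later analysis plan could not repair it. At stake is the comparison of uMARS scores across dermatology background, which is one of only two associations the article expects to find.

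**Working it through.** **Inputs from the article.** The three answers are in Demographic Variables. The Sample Size Calculation starts from 100 participants and states that "we assume a dropout rate of 50" percent, so 100 × (1 − 0.50) = 50, which reproduces the article's final number. The totals of 48 and 98 elsewhere in the article are a separate matter and play no part here. The article gives no effect size, no standard deviation and no expected distribution over the three levels. Every such figure below is an assumption.

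**Step 1: coverage.**

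| Training | Experience | Offered? |
|---|---|---|
| yes | yes | yes (top level) |
| no | yes | yes (middle level) |
| no | no | yes (bottom level) |
| yes | no | no |

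**Step 2: what can be estimated if everyone is placed correctly.**

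- Top minus middle gives the effect of training among experienced workers.
- Middle minus bottom gives the effect of experience among untrained workers.
- A model with an intercept, training and experience has rank 3 of 3 on the three offered cells, so both effects are identified if they are additive.
- Adding the interaction gives rank 3 of 4. Training among the inexperienced, experience among the trained and the interaction are not estimable. With all four cells the rank is 4 of 4.

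**Step 3: dilution of the top-to-bottom contrast.** Let dT and dE be additive effects of training and experience in the same direction, with dT + dE = 0.60 points. Let 15 respondents truly belong in the top level and 10 in the bottom level, and let m trained-only workers all tick the same level.

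- All tick the top level: contrast = 0.60 − [m/(15 + m)] × dE
- All tick the bottom level: contrast = 0.60 − [m/(10 + m)] × dT

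The effect that enters each formula is varied from 0.2 to 0.4.

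| m | Fraction, top | Contrast, top | Fraction, bottom | Contrast, bottom | Loss |
|---|---|---|---|---|---|
| 0 | 0 | 0.60 | 0 | 0.60 | nil |
| 2 | 2/17 | 0.58 to 0.55 | 2/12 | 0.57 to 0.53 | about 4–11% |
| 8 | 8/23 | 0.53 to 0.46 | 8/18 | 0.51 to 0.42 | about 12–30% |

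For example, with m = 8 at the bottom level and dT = 0.4: 0.60 − (8/18) × 0.4 = 0.42, and 0.18/0.60 = 30%.

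**Step 4: dilution of the single-factor contrasts.** Assume dT = dE = 0.5, a share f of the sample trained only, and the rest spread equally, so r = (1 − f)/3 in each offered cell. If the trained-only workers tick the top level, the training contrast is 0.5 − [f/(r + f)] × 0.5. For f = 5%, 10% and 20% (2.5, 5 and 10 of 50) it is 0.43, 0.38 and 0.29. If they tick the bottom level, the experience contrast falls to the same values.

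**Step 5: the middle level.** If they tick the middle level, the top-to-bottom contrast does not change. Only its division between training and experience shifts, and only when the two effects differ. With dT = 0.5, dE = 0.3 and f = 20%, the two contrasts become 0.41 and 0.39, which still sum to 0.80.

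**The case against.** The strongest objection is the eligibility rule. A trained worker who deals with skin NTDs daily can truthfully claim experience, so the missing cell may be small or empty. This limits the likely bias. It does not make the list complete: the form itself foresees inexperienced respondents, since it offers a neither-trained-nor-experienced level and a caseload below one per month. The tension between that caseload answer and the daily-contact rule is a separate matter, and it does not show that trained-but-inexperienced workers will enrol.

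Second, exposure is also captured by the caseload item, and the Results section speaks of dermatology variables in the plural. That helps in part. The caseload item covers skin NTDs, not all dermatology, and it cannot show whether a respondent was placed wrongly on training.

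Third, the losses are modest beside sampling error. For 15 versus 18 respondents and an assumed standard deviation of 0.5 to 0.8, the standard error is SD × √(1/15 + 1/18), or 0.17 to 0.28. The loss at m = 8 is 0.07 to 0.18. This stands, and it is one reason to rate the point as minor.

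Fourth, the article nowhere states an aim of separating training from experience. This also stands. The point therefore rests on the incomplete answer list, not on an unmet aim of separation.

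**Conclusion.** The answer list is incomplete for one of the two suspected determinants. A trained but inexperienced worker has no true answer, and the error cannot be corrected at analysis. Two conditional effects and the interaction are not estimable, and misplaced respondents weaken the contrasts that remain, more so the more of them there are.

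The size is unknown. Under the assumed 0.60-point contrast and group sizes, the loss is nil for 0 such workers, about 4–11% for 2 and about 12–30% for 8. These figures rest on additive effects in the same direction and on all such workers choosing the same end level.

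A reader might infer that training cannot be separated from experience at all. The documents do not support that: if nobody falls in the missing cell, the three levels give one contrast for each, and both effects are identified under additivity. Nor should the 12–30% be read as the expected loss, since the 8 of 50 behind it is an assumption.

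The overall uMARS score is unaffected. The point is minor: it touches a secondary comparison in a small, prototype-stage, non-probability sample.

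**What to change.** Before the form goes live, either add a fourth answer, 'Trained but without experience with dermatology patients', or replace the item with two yes/no questions, one on dermatology training and one on experience with dermatology patients. Either change makes the list complete. The fourth answer is the smaller edit; two questions let training and experience enter the analysis as separate factors. If the fourth group proves empty, the two questions give the same information as the present item. If it is very small, the interaction will be poorly estimated, but nobody will have been misplaced.

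The cost is one extra survey line and no extra participants.

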#### uMARS Questionnaire

The uMARS is a simple, objective, and reliable tool developed for users by Stoyanov et al [12] to classify and assess the quality of health-related mobile apps. The tool assesses 20 items clustered into 4 objective subscales (engagement, functionality, aesthetics, and information quality) and 1 subjective subscale. Participants rate each item using a Likert scale from 1 to 5 (1=“Inadequate,” 2=“Poor,” 3=“Acceptable,” 4=“Good,” and 5=“Excellent”). There is also the option “not applicable” if an item cannot be assessed. There is an extra category entitled *App-Specific* with descriptive purposes only that contains 5 more items and can be adjusted and adapted by researchers. This category evaluates the perceived impact of the app on users’ knowledge, attitudes, intentions to change, and the likelihood of actual change. We will add 9 questions to complete this domain, relating to app discovery, time using the app, frequency of use, notification updates, usefulness, translation features, patient record features, and desktop version.

The uMARS score is calculated separately based on the original recommendation from the authors of this scale. Hence, 2 scores will be obtained: app quality mean score and app subjective quality score. This division is made to strengthen the objectivity of the uMARS as a measure of app quality. All those questions rated as “not applicable” will be excluded from the mean scores.

#### Semistructured Interviews

Semistructured interviews are a validated qualitative method for exploring the perspectives, perceptions, and opinions of participants. Semistructured interviews combine prepared questions with others that arise during the interview [18].

In this study, interviewers will ask 8 questions in the same order and using the same words to each participant—a standardization that will facilitate comparability [19]. Questions will be open-ended, neutral, clear, and in familiar language. The structure of the interviews will be as follows: a brief presentation of the interviewer and the study, a general question related to the overall use of Skin NTDs App, 8 core questions directly relating to information needed for app assessment, and unplanned questions that arise during the interview based on the participants’ answers.

It is estimated that semistructured interviews will be conducted in a minimum of the 10% of the final sample size or until information saturation is reached.

### Data Collection and Study Procedure

Once a participant has signed the initial consent form, an email will be sent with the first part of the survey and details of the study procedure. This information will include the following: links to download the app, a recommended time of app usage before answering the survey, and information about the interviews.

Participants will receive an email over the following days with a Google Forms link through which they can enter their demographic data and answers to the uMARS questionnaire. In the last section of the survey, participants will need to indicate whether they would like to participate in the next phase of the study—the semistructured interviews.

A separate email or WhatsApp message will be sent to those who wish to participate in the interviews. Participants will receive an information sheet and a second consent form, which must be signed and returned before the participant can be interviewed.

Once informed consent has been obtained, participants and researchers will schedule a semistructured interview at a mutually convenient time. Interviews will be carried out via video calls using Google Meets; therefore, participants will receive an email or WhatsApp message with a link specifying a date and time.

Once the interviewer has reminded the interviewee why audio recording is necessary, audio recording will start and continue throughout the interview. The questions will be asked as previously described (for more detail, see Multimedia Appendix 2). Interviews will last between 25 and 40 minutes, during which time the interviewer will take notes and repeat questions or words as required to fully understand the interviewee’s meaning.

Researchers will use Otter.ai software to transcribe all interviews for analysis. During the data collection phase of the study, researchers will send as many reminders to participants as they deem necessary.

### Statistical Analysis

Quantitative data will be collected in Excel (Microsoft Inc) to be analyzed using SPSS for Windows (version 25; SPSS Inc). Statistical significance for all tests will be set at a *P* value of ≤.05. To describe the quantitative information received from the uMARS scores, a descriptive analysis will be carried out. Measures of frequency, central tendency, and dispersion will be used to describe this data, which will be shown in tables. Depending on sample size, a Shapiro-Wilk or Kolmogorov-Smirnov test will be used to assess the normality of data (*P*≤.05). In the bivariate analysis, a chi-square test will be used to compare categorical variables. Depending on whether the distribution is normal, quantitative data will be compared using a Student *t* or Mann-Whitney *U* test. A multivariate analysis will be performed using a logistic regression analysis to add the covariates that could skew the main association under analysis. Finally, a cluster analysis will be performed to identify similar groups based on the observed values of several variables. A 95% CI will be assumed and *P*≤.05 will be considered to indicate a significant difference.

Selected quotes will be returned to participants for approval. Qualitative data derived from the semistructured interviews will be analyzed using ATLAS.ti (Scientific Software Development GmbH). We will identify attributes, cluster them into different themes, and then code these themes to analyze the various dimensions explored during the interviews.

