**Methods:**

A cross-sectional study will be conducted in 2 LMICs: Ghana and Kenya. We will use snowball sampling recruitment to select 48 participants from the target population of all FHWs dealing with skin NTDs. The sample group of FHWs will be asked to download and use Skin NTDs App for at least 5 days before answering a web-based survey containing demographic variables and the user Mobile App Rating Scale (uMARS) questionnaire. A semistructured interview will then be conducted. Quantitative and qualitative data will be analyzed using SPSS (version 25; SPSS Inc), with statistical significance for all tests set at a 95% CI and *P*≤.05 considered significant. Data derived from the semistructured interviews will be clustered in themes and coded to enable analysis of various dimensions using ATLAS.ti.

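### The test-selection rule for the uMARS score looks only at normality; with unbalanced subgroups of unequal spread its false-positive rate could be about 10%-15%, or about 1%, instead of 5%

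*Protocol article*

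**What the plan says.** The Statistical Analysis section sets a two-step rule. First, "Depending on sample size, a Shapiro-Wilk or Kolmogorov-Smirnov test will be used to assess the normality of data", at a P value of .05. Then, "Depending on whether the distribution is normal, quantitative data will be compared using a Student" t test or a Mann-Whitney U test. The threshold is common to everything: "Statistical significance for all tests will be set at a" P value of .05 or below. No check of equal variance and no unequal-variance test is named. The text does not say whether normality is judged once for the uMARS score, separately for each factor, or within each group.

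The tests serve the secondary goal in the Introduction, which is to find out "whether any of the demographic information collected has an impact on the final uMARS score". On numbers, the Sample Size Calculation starts from the upper limit ("Taking into account that 100 is the maximum recommended number of participants"), adds "we assume a dropout rate of 50"%, and concludes: "These calculations leave a final sample size of 50 participants".

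**The concern.** A rule that asks only about normality leaves out the assumption that matters most when group sizes differ. Student t pools the two variances. If the smaller group is the more variable, the pooled standard error is too small; if it is the less variable, too large. Mann-Whitney does not repair this, because it is not a test of equal means and its null distribution also assumes the same spread in both groups.

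Imbalance is plausible here. Snowball sampling gives no control over how factors split. Respondents must own a smartphone and have used the app on five days, so people with low mobile-technology knowledge may be few. The score is bounded at 1 and 5, so a group close to the ceiling may vary less than another.

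What is at stake is which user characteristics are reported as affecting the score. The Introduction ties that question to the developers' intention not to customize the app by setting. The Results section predicts no difference for some factors and suspects one for dermatology experience and mobile technology. A rule that rejects too often or too rarely, depending on which group is more variable, is a weak basis for either statement.

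**Working it through.** **The plan's own figure.** 100 × (1 − 0.50) = 50, as stated. The abstract gives 48 ("We will use snowball sampling recruitment to select 48 participants") and Study Design gives 98. I use 50. Using 48 changes nothing material. The pooling error below depends on the proportional split rather than on the total, so 98 would not remove it.

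**Inputs.** From the article: N = 50, threshold .05 (taken as two-sided), and the two-step rule. Assumed, because the article gives none of them: a 40/10 split; SD 0.5 in the larger group with 0.75 or 0.9 in the smaller (ratio 1.5 or 1.8), and the reverse; no true mean difference.

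**Approximate size of Student t.** The pooled variance is sp² = [(n₁−1)s₁² + (n₂−1)s₂²]/(n₁+n₂−2), and the test uses SE = √[sp²(1/n₁+1/n₂)]. The true SE is √(s₁²/n₁ + s₂²/n₂). With critical value 2.011 (48 df), the rejection rate is about 2[1 − Φ(2.011 × pooled SE/true SE)].

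- SD 0.5 (n = 40) and 0.75 (n = 10): sp² = (39×0.25 + 9×0.5625)/48 = 0.3086; pooled SE = √(0.3086×0.125) = 0.196; true SE = √(0.25/40 + 0.5625/10) = 0.250; ratio 0.786; 2.011×0.786 = 1.58; rate about 11.4%.
- SD 0.5 and 0.9: sp² = (9.75 + 7.29)/48 = 0.355; pooled SE 0.211; true SE 0.295; ratio 0.713; rate about 15.2%.
- SD 0.75 (n = 40) and 0.5 (n = 10): sp² = (39×0.5625 + 9×0.25)/48 = 0.504; pooled SE 0.251; true SE 0.198; ratio 1.27; rate about 1.1%.
- Equal SDs, or equal group sizes: the ratio is 1 and the test is close to nominal.

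**Simulation of the full rule.** 3,000 replicates per row, split 40/10, equal means. Shapiro-Wilk at .05 on all scores together, then Student t if normal, otherwise Mann-Whitney. Skewed data are 5 minus a gamma variable with mean 1. Monte Carlo error is about 0.4 points near 5% and 0.6 near 12%.

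| Data | SD, n=40 / n=10 | Student t alone | Mann-Whitney alone | Planned rule | Welch |
|---|---|---|---|---|---|
| Normal | 0.5 / 0.5 | 5.3% | 4.7% | 5.3% | 5.2% |
| Normal | 0.5 / 0.75 | 12.4% | 8.0% | 11.2% | 5.5% |
| Normal | 0.5 / 0.9 | 14.9% | 9.3% | 12.4% | 4.4% |
| Normal | 0.75 / 0.5 | 1.2% | 2.1% | 1.2% | 4.9% |
| Normal | 0.9 / 0.5 | 0.5% | 1.6% | 0.5% | 5.0% |
| Skewed | 0.5 / 0.5 | 4.7% | 4.6% | 4.8% | 5.5% |
| Skewed | 0.5 / 0.75 | 11.3% | 10.8% | 10.6% | 7.3% |
| Skewed | 0.5 / 0.9 | 14.5% | 13.5% | 13.4% | 7.7% |
| Skewed | 0.75 / 0.5 | 2.3% | 4.1% | 4.1% | 5.1% |
| Skewed | 0.9 / 0.5 | 1.3% | 5.7% | 5.6% | 4.9% |

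Other runs of the scenarios with the more variable small group put the planned rule at 10.5%-14.3% on normal data and 9.8%-16.4% on skewed data. Welch was at 4.8%-5.3% and 6.7%-9.5%.

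**Sensitivity to the assumptions (normal data).** At 25/25 with SD ratios from 0.5 to 2, the planned rule stays at 4.9%-5.7%. At 30/20 with ratio 1.5 it is 6.2%-6.5%. If normality is tested within each group instead, the 40/10 rate is 13.7% at ratio 1.5 and 18.1% at ratio 2 (12.3% and 14.1% with the pooled check).

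**The case against.** The best reply is that the size of the problem comes wholly from assumed inputs. The article gives no subgroup sizes, SDs or SD ratios. Imbalance alone does nothing, and 10% is reached only with roughly a 4:1 split, an SD ratio of about 1.5 or more, and the larger SD in the smaller group. That stands, and it is why the point is conditional.

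A second reply is that the tests support a secondary goal in a prototype-stage survey whose main output is descriptive. That also stands.

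A third is that Welch is not exact either. For skewed scores with a more variable small group it runs at about 7%-8%. True, but the planned rule is at 10% or more in the same data.

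A fourth is that an article may leave variance options to the full protocol or analysis plan. This carries less weight: the article does not leave the choice open but fixes both tests and the criterion for switching.

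A reader might go further and blame the pre-test itself. The figures do not support that. With equal spread the gate does no visible harm, and on normal data with unequal spread Student t without any gate does somewhat worse (12.4% against 11.2%, and 14.9% against 12.4%). A reader might also infer that the method turns on one or two respondents around n = 50, where one normality test replaces the other. The article states no threshold, so that has no basis in the text; nor does it say whether the Kolmogorov-Smirnov test would be corrected for estimated parameters, on which any contrast between the two tests depends.

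**Conclusion.** The point holds in conditional form. The stated rule chooses its test on normality alone, and neither branch copes with unequal variances in unbalanced groups. Under an assumed 40/10 split of 50, the chance of a false difference in means would be about 10%-15% if the smaller group has 1.5-1.8 times the SD, about 1% on normal data if it is the less variable, and about 5% if spreads are equal. For skewed scores with a less variable small group the rule was not clearly conservative (4.1% and 5.6%).

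It would be wrong to say that small unbalanced subgroups will as a rule see 10%-15%: that needs the SD difference as well, in that direction. It would also be too strong to say that factors will be reported on different effect scales. That happens only if normality is judged factor by factor or group by group; judged once on the score, every two-group factor gets the same test, and the article does not say which is meant. The point is worth acting on because the remedy is cheap. It does not touch the descriptive assessment of the app.

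**What to change.** Remove the normality gate from the Statistical Analysis section and state one method in advance for the uMARS score:

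- for every two-group comparison, the mean difference with a Welch 95% CI and P value;
- for factors with three or more levels, among them dermatology experience, mobile-technology knowledge and working institution, Welch ANOVA or a linear model with HC3 standard errors. The two tests now named compare only two groups;
- Mann-Whitney as a stated sensitivity analysis.

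Removing the gate while keeping Student t would not help; the change to an unequal-variance method is the essential part. The cost is a wording change, with no extra data. There is a very small loss of power when variances are equal, and the article should acknowledge that Welch can remain somewhat above 5% when scores are skewed and the small group is the more variable one.

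### The bivariate plan names only two-group tests for the uMARS scores, but six of the eight categorical factors, including both suspected determinants, have three or four levels

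*Protocol article*

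**What the plan says.** The end of the Introduction sets, as a secondary goal, finding out whether any of the collected demographic characteristics influences the final uMARS score. The uMARS Questionnaire section makes the outcome quantitative: "2 scores will be obtained: app quality mean score and app subjective quality score", each built from items rated 1 to 5.

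The Statistical Analysis section names the bivariate tests. For categorical data, "a chi-square test will be used to compare categorical variables". For scores, the text reads: "Depending on whether the distribution is normal, quantitative data will be compared using a Student" t or Mann-Whitney U test. The threshold is common to everything: "Statistical significance for all tests will be set at a" P value of ≤.05. The section mentions no adjustment for multiple comparisons and no test for more than two groups. The multivariate step is a logistic regression.

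The Demographic Variables section gives most factors more than two answers. For dermatology, for example, the middle of three options is "Not trained but with experience with dermatology patients". The Results section then says which factors the authors have in mind: "those variables related to experience in dermatology or the use of mobile technology may be determining factors".

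**The concern.** The Student t and Mann-Whitney U tests each compare two groups, so neither can compare a score across three or four groups in one test. The mismatch covers most of the listed factors and both of those the authors single out.

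An analyst holding to the text has two ways forward. One is to test pairs of levels, each at .05, which raises the chance of a spurious finding within a factor. The other is to merge levels, or to split the score, at points that the article does not fix and that could be chosen after the data are seen.

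The answer matters because the Introduction ties this goal to the developers' intention not to customise the app by setting. A false positive could suggest a need for tailoring that does not exist.

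**Working it through.** **Sample size used.** The Sample Size Calculation section starts from 100 participants and a 50% dropout: 100 × (1 − 0.5) = 50, which reproduces its figure. The Abstract gives 48 participants, and Study Design gives 98, which after the same dropout leaves 98 × 0.5 = 49. The check therefore uses a total of 48 to 50.

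**Levels per factor, from Demographic Variables.**

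| Factor | Levels | Pairs, k(k−1)/2 |
|---|---|---|
| Gender | 4 | 6 |
| Type of health worker (three named plus Other) | 4 | 6 |
| Frequency of dealing with skin NTDs | 4 | 6 |
| Dermatology experience and training | 3 | 3 |
| Knowledge of mobile technology | 3 | 3 |
| Working institution | 3 | 3 |
| Country | 2 | 1 |
| Work environment | 2 | 1 |

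Six of eight factors (75%) have more than two levels. Age (no response format given) and languages (open answer) are not counted.

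**Error within one factor if all pairs are tested at .05.** If the m tests were independent, the familywise error would be 1 − 0.95^m:

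- three levels, m = 3: 1 − 0.95³ = 0.143;
- four levels, m = 6: 1 − 0.95⁶ = 0.265.

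Pairwise tests share groups and so are correlated, which makes these figures too high. Simulation with no true difference and normal data (10,000 runs for t and ANOVA, 5,000 for Mann-Whitney and Kruskal-Wallis) gave:

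| Group sizes | Any pairwise t | Any pairwise Mann-Whitney | ANOVA | Kruskal-Wallis |
|---|---|---|---|---|
| 17, 17, 16 | 0.122 | 0.121 | 0.051 | 0.049 |
| 16, 16, 16 | 0.123 | 0.121 | 0.050 | 0.048 |
| 30, 15, 5 | 0.120 | 0.113 | 0.052 | 0.049 |
| 13, 13, 12, 12 | 0.199 | 0.193 | 0.046 | 0.042 |
| 12, 12, 12, 12 | 0.199 | 0.185 | 0.049 | 0.048 |

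A separate simulation of pairwise t tests gave 0.126 for three groups of 17 and 0.202 for four groups of 13. Taken together, the error is about 11-13% for three levels and 18-20% for four. One overall test per factor brings it back to about 5% or slightly below.

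**Do the other named methods fill the gap?** Chi-square takes multi-level factors but needs a categorical outcome, and the uMARS scores are means. Logistic regression also takes multi-level factors but needs a categorical outcome, and the article gives no cut-off for the score. The value above 3 in the Results section is an expected result, not an analysis threshold.

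**The case against.** The strongest reply is that the factors are not untestable. Logistic regression can carry multi-level factors and age, and levels can be merged so that a two-group test applies. A reader might infer from the mismatch that the plan cannot address these factors at all. That goes too far, because these routes exist. What remains is that the article states neither a score cut-off nor a merging rule, so both routes are left open to choices made after seeing the data.

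It is also fair to say that the article nowhere announces all-pairs testing, and that not every level will necessarily fill. Eligibility requires daily work with skin NTDs, which sits badly with the lowest frequency category. Participants own a smartphone and have used the app on five days, so low mobile-technology knowledge may be rare. Gender may reduce to two levels, which alone would leave five of eight factors with more than two. The percentages above therefore illustrate one way of following the text and are not the plan's error rate. For the same reason, adding up the pairs over all factors into one large count of tests is not supported. Thin levels do not remove the problem, though: they make unplanned merging more likely.

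Two further inferences should be resisted. Small expected counts in chi-square tables are not a finding here, because the article specifies no such table and the goal concerns a quantitative score. Nor can it be said that age is continuous and has no method: its format is not given, and it could enter the regression.

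Finally, the missing tests might be put down to the brevity of an article. That does not hold, because the article names specific tests and they do not fit its own factors.

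**Conclusion.** The point stands as a mismatch between the named tests and the factors they are meant to serve. It affects six of eight categorical factors as listed, including both suspected determinants. The level counts come directly from the article. The error figures (about 11-13% and 18-20% within a factor) assume all-pairs testing at .05, about 50 participants, normal scores and all levels filled.

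It should be fixed, but it does not threaten the study. A reader might infer that the app-quality assessment itself is undermined. It is not: that main aim is served by descriptive statistics. The affected goal is secondary, in a prototype-stage snowball sample whose limited representativeness the authors acknowledge.

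**What to change.** In the Statistical Analysis section:

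- Keep the t or Mann-Whitney test for country and work environment.
- For every factor with more than two levels, name one test per factor: one-way ANOVA or, where normality fails, Kruskal-Wallis. Allow pairwise comparisons only as follow-up, adjusted for multiplicity.
- Optionally, use a trend test for the ordered factors (dermatology experience, mobile-technology knowledge, frequency). Its small downside is that it assumes a monotone effect, and the Results section states no direction.
- If levels may be merged or the score dichotomised, state the rule before the data are seen.

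The cost is a few sentences, with no extra participants or data. One test per factor controls the error within a factor, not across factors or the two scores, so the results should still be read as exploratory.
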